## Substudies

### Caretaker surveillance study.

This has been submitted as a separate protocol to DMID, COMREC and the University of Maryland IRB.

### Pharmacokinetics substudy

Participants who develop malaria again after enrollment in the study will be eligible to participate in a pharmacokinetics substudy. In this study, we will collect two additional blood specimens to describe the pharmacokinetics profiles of the partner drugs. This understanding of the pharmacokinetic profile is an important key to understanding observed efficacy, or lack of efficacy, in each treatment arm. Participants will be randomly assigned to have blood drawn at for drug levels two time points after drug administration to capture the time to the maximum concentration (Tmax) and the maximum concentration (Cmax) and to characterize the elimination phase. In addition, we will use a portion of the serum collected during the routine venipuncture on day 0, for the collection of parasites, to measure baseline drug levels in the blood.Serum from these time points will also be used to conduct bioassays to determine the relationship between pharmacokinetics and pharmacodynamics of the drugs. At this time, we have funding to begin preliminary analysis of these specimens, through a University of Maryland Intramural New Investigator Award to [name]. [name] has submitted a grant to NIAID to support the full analysis of these samples. It is necessary to begin collection of these samples during the study, even if there is a delay in obtaining the funding to conduct the analysis.

Participants will be randomly assigned to two time points for additional 3 cc venous sampling based on their partner drug assignment. In the artesunate arm, levels will be measured from 30 minutes to four hours after a dose. In the azithromycin arm, levels will be measured three hours after the dose, before the second or third dose or on follow up days 3, 7, 14, 21, 28. In the atovaquone-proguanil arm, participants will be assigned to levels at one to three hours after a dose, before the second or third dose or follow up days 3, 7, 14, 21, 28. The sampling scheme for atovaquone proguanil reflects the need to capture the pharmacokinetic characteristics of both drugs.

Participation in this study will be optional for individuals who enroll in the longitudinal trial. They will be offered participation only during an episode of malaria after the first and it will be clearly explained that their decision does not affect their participation in the longitudinal trial. Although this substudy will be mentioned in the initial informed consent process, a separate informed consent process will occur when the participant is eligible for this substudy. Because the children who are enrolling in the study are acutely ill with malaria, we do not want to prolong the informed consent process to describe this portion of the study. In addition, those participants randomly assigned to chloroquine alone will not be eligible. The informed consent process will be conducted in the manner described in Section 14.

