### Pharmacokinetics

|  | **Chloroquine (26)** | **Artesunate (27;28)** | **Azithromycin (29;30)** | **Atovaquone-Proguanil (31)** |
| --- | --- | --- | --- | --- |
| **Metabolite** | Desethylchloroquine (partial) | Dihydroartemesinin | None | A: None identified  P: Cycloguanil |
| **Clearance** | Hepatic and renal | Unknown | Biliary | A; Biliary  P: Renal |
| **Half-life** | 7-10 days | ≤ 1 hour | 68 hours | A: 2-3 days  P: 12-21 hours |
| **Maximum time point when drug level sufficient for antimalarial activity has been detected** | Up to 70 days | Median 8 hours but >24 has been reported | Unknown, 14 days for bacterial infection | Up to six weeks (atovaquone) |

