## Drug administration

After laboratory tests have been completed and all the eligibility criteria are met, the participant can be enrolled. After enrollment and assignment of as participant ID number, the participant will be escorted to the study pharmacy. Drug assignment will be made as described in the randomization section. The drug doses are as follows:

Chloroquine 10 mg/kg on days 0 and 1; 5 mg/kg on day 2 (to the nearest ¼ tablet)

Artesunate approximately 4 mg/kg on days 0, 1 and 2

Azithromycin 30 mg/kg on days 0, 1 and 2

Atovaquone-proguanil approximately 15-20 mg/kg on days 0, 1 and 2 (as described in the study intervention section and directed in the package insert)

Participants will be observed for at least 30 minutes to monitor for adverse reactions and to make sure the medicine is not vomited. All drug administration attempts and episodes of vomiting will be recorded on the CRF. The procedure for drug administration will be as follows:

1. Administer dose of chloroquine and observe for 30 minutes.
   1. If vomiting does not occur, go to step 2
   2. If vomiting occurs after first dose, repeat dose
   3. If vomiting occurs after second dose, consult a clinician or investigator
   4. If the clinician determines that the child appears well enough to continue with oral therapy, repeat dose
   5. If third dose is vomited within 30 minutes, transport to hospital for evaluation and parenteral therapy.
      1. If this sequence of events occurs on day 0 of the enrollment illness, the participant will be removed from the study
      2. If this sequence of events occurs on day 1 or 2 of the enrollment illness or during subsequent treatment episodes, the participant will continue in the study
2. If the participant has tolerated the chloroquine and is assigned to receive combination therapy, administer the partner drug next.
   1. If vomiting does not occur, administration complete
   2. If vomiting occurs after first dose, repeat dose
   3. If vomiting occurs after second dose, consult a clinician or investigator
   4. If the clinician determines that the child appears well enough to continue with oral therapy, repeat dose
   5. If third dose is vomited within 30 minutes, do not administer drug again and note on CRF
      1. If this sequence of events occurs on day 0 of the enrollment illness, the participant will be removed from the study

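### The pharmacokinetics substudy aims to capture Tmax and Cmax, but azithromycin has one nominal post-dose draw time (three hours), so its peak cannot be located

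*Protocol*

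**What the plan says.** The Pharmacokinetics substudy (Protocol, section 4.4) states its scale and purpose: "we will collect two additional blood specimens to describe the pharmacokinetics profiles of the partner drugs". Each child is randomly assigned two sampling times, and the purpose of those times is "to capture the time to the maximum concentration (Tmax) and the maximum concentration (Cmax) and to characterize the elimination phase". No partner drug is exempted from this aim.

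The post-dose times then differ by arm:

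- Artesunate: "In the artesunate arm, levels will be measured from 30 minutes to four hours after a dose".
- Atovaquone-proguanil: "participants will be assigned to levels at one to three hours after a dose", plus pre-dose and follow-up days. The protocol explains that this scheme reflects the need to cover both components.
- Azithromycin: "In the azithromycin arm, levels will be measured three hours after the dose, before the second or third dose or on follow up days". Those days are 3, 7, 14, 21 and 28. No reason is given for the single post-dose time.

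The Drug administration section gives the dosing days: "Azithromycin 30 mg/kg on days 0, 1 and 2". The Pharmacokinetics table in the background gives azithromycin a half-life of 68 hours. Its entry for how long antimalarial levels persist is "Unknown, 14 days for bacterial infection".

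**The concern.** Random assignment of sparse samples works because different children fill in different parts of the concentration curve, and the pooled data then trace the whole curve. For azithromycin the draws near the peak all share one nominal time. Pooling more children makes the average three-hour level more precise, but adds nothing about whether the peak came before or after three hours.

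Two of the three stated parameters are affected for one of the three partner drugs. Tmax would have no support in the data, and Cmax would be the three-hour level under another name. Sampling times are fixed in the protocol, so this cannot be left to the analysis plan.

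**Working it through.** The protocol states no sample size, precision or expected Tmax for this substudy, so there is no figure to reproduce. The check is whether the listed times can identify the peak.

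**Inputs from the protocol.** Azithromycin doses on days 0, 1 and 2 (0, 24 and 48 h). Draws at 3 h after a dose, before dose 2 or 3 (about 24 h after the previous dose), and on days 3, 7, 14, 21 and 28. Half-life 68 h. **Assumed, because the protocol gives none:** the absorption rate ka, shown as a range, and the distribution parameters in step 2.

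**Step 1. One compartment, first-order absorption.** ke = ln 2 / 68 = 0.0102 per hour. Tmax = ln(ka/ke)/(ka − ke). In units of dose over volume, C(t) = ka/(ka − ke) × (e^(−ke·t) − e^(−ka·t)).

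| ka (per h) | Tmax (h) | C(3 h) | C(24 h) | C(3 h)/C(24 h) |
|---|---|---|---|---|
| 0.5 | 7.95 | 0.762 | 0.799 | 0.95 |
| 1 | 4.63 | 0.930 | 0.791 | 1.18 |
| 2 | 2.65 | 0.972 | 0.787 | 1.24 |
| 5 | 1.24 | 0.972 | 0.785 | 1.24 |

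For ka from 1 to 5, Tmax moves from 4.6 h to 1.2 h, while the three-hour level moves only from 0.93 to 0.97 and its ratio to the trough from 1.18 to 1.24. Slow absorption (ka = 0.5) would show in that ratio, but only if this simple curve shape is taken as true.

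**Step 2. Two compartments.** An illustrative model (ka 0.7, k10 0.06, k12 0.25, k21 0.028 per hour, V = 1) was evaluated without noise at the protocol's times. Then ka was fixed at other values and the remaining four parameters refitted.

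| ka fixed (per h) | Largest misfit (log scale) | Tmax (h) | Cmax (relative) |
|---|---|---|---|
| 0.35 | 0.0000 | 2.35 | 0.512 |
| 0.5 | 0.0000 | 2.46 | 0.507 |
| 0.7 | 0.0000 | 2.13 | 0.527 |
| 1.0 | 0.0000 | 1.76 | 0.572 |
| 1.5 | 0.0000 | 1.36 | 0.652 |
| 2.5 | 0.0000 | 0.98 | 0.775 |
| 4 | 0.0000 | 0.71 | 0.877 |

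The same data fit Tmax from 0.7 to 2.5 h and Cmax from 0.51 to 0.88.

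**Step 3. Why this does not hinge on the chosen values.** In the illustrative model s = 0.06 + 0.25 + 0.028 = 0.338 and r = √(0.338² − 4 × 0.06 × 0.028) = 0.328. The fast rate is (s + r)/2 = 0.333 per hour, and by 24 h its term has shrunk to e^(−0.333 × 24) = 0.0003. Every draw except the three-hour one therefore lies on the terminal line and fixes only its height and slope. The three-hour level adds one more quantity. Three quantities cannot determine five unknowns (ka, k10, k12, k21, V).

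The slow rate here is (s − r)/2 = 0.00505 per hour, a terminal half-life of about 137 h rather than the protocol's 68 h. The counting argument does not use the terminal half-life, but the Tmax and Cmax ranges in step 2 are illustrations, not predictions.

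**The case against.** **A model could return values.** A one-compartment form, or an absorption rate fixed from outside, would yield a Tmax and Cmax from this schedule. That is so, but the result would come from the assumption, while the protocol says the sampling is meant to capture these parameters.

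**Three hours is a nominal time.** Actual draw times will scatter, and recorded times would carry some information. The scatter is unplanned, however, and the arm has no window like those in the other two.

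**Atovaquone-proguanil needs a window because it contains two drugs.** The protocol says so. Artesunate is listed as one drug and still has a window.

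**Persistence matters more than the peak for azithromycin.** The Rationale does stress how long the partner drug stays active, and the elimination phase is well sampled. This limits the importance of the point without removing the mismatch between aim and schedule.

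**Stronger readings a reader might infer.** First, that the day 21 and 28 draws are wasted. At a 68 h half-life, counted from the last dose, 2^(−(21 − 2) × 24/68) = 0.96% remains on day 21 and 2^(−(28 − 2) × 24/68) = 0.17% on day 28. Yet elimination is a stated aim, the table lists antimalarial persistence as unknown, no assay limit is given, and these are existing visits. A small remaining fraction does not show that a draw is useless. Nor can the share of draws on those days be stated, because the slot weights are not given. Second, that the three-hour level misses Cmax by a known amount. The documents give no absorption rate, so the size of any error is not established. Third, that the exposure–efficacy comparison fails in this arm. The protocol does not say that comparison uses Cmax, and trough levels, late levels and bioassays also describe exposure.

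**Conclusion.** The point holds in a narrow form. The substudy sets out to capture Tmax and Cmax for the partner drugs but gives azithromycin one nominal post-dose time. Without an outside assumption about the curve, azithromycin Tmax cannot be estimated, and the three-hour level equals Cmax only if the peak is taken to fall there. This conclusion rests on the listed times. The Tmax and Cmax ranges in the working rest on assumed absorption and distribution rates and only illustrate it.

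Severity is minor. The substudy is optional, partner-drug pharmacokinetics is not among the trial's listed objectives, and the primary endpoint is unaffected.

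**What to change.** In the Pharmacokinetics substudy section, replace the single three-hour azithromycin time with randomly assigned post-dose times over a window, for example one to four hours. Keep two samples per child, the pre-dose times and all follow-up days, including days 21 and 28. Record the actual draw time.

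Four hours is the longest post-dose time already used in the artesunate arm. If the true peak is later than that, as in the ka = 0.5 row of the working, the window would show levels still rising but would not reach the peak. The protocol should acknowledge this.

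If the window is not adopted, drop Tmax as an azithromycin aim and describe the peak measure as the three-hour level.

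The cost is a change to the substudy assignment list and its instructions, with no extra blood or assays. The downside is varied clinic waiting times, longer for some children than the present three hours.

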### Endothelial adhesion and malaria pathology substudy

This study is funded through a grant to [name] of the Malawi-Liverpool-Wellcome Trust Clinical Research Programme (MLW) from the Gates Malaria Partnership. This is being included as a substudy for this protocol because the specimens already being collected from this study can be used for this study and we can avoid multiple blood draws from small children. [name] is a talented, enthusiastic post-doctoral fellow who would otherwise not have access to specimens from cases of uncomplicated malaria that he requires for his study. The University of Maryland, Blantyre Malaria Project and MLW have had a long-standing collaboration and we see our participation in this project as part of the research cooperation that we have enjoyed for many years.

The study requires parasites from well-characterized malaria episodes. The parasites collected from episodes of malaria during the longitudinal trial will serve as uncomplicated malaria parasites to compare with parasites collected from patients with severe disease. No extra specimens will be collected for this substudy and there will be no additional cost to the study. We have added a sentence to the informed consent document to reflect the use of the parasites to understand more about the pathology of malaria. This study has already been approved by the College of Medicine Research and Ethics Committee of the University of Malawi.

**Background**

Previous studies have demonstrated that nearly all patient isolates of *Plasmodium falciparum* are able to bind CD36 and that ability to bind ICAM-1 is also common. Newbold and colleagues found that approximately 80% of patient isolates were able to bind ICAM-1 (55). Other studies have shown that patient isolates may bind to multiple host receptors (56;57). Recently, we have shown that competition does occur on endothelium between different *P. falciparum* parasite lines, and that laboratory isolates could be ranked for their efficiency of binding to epithelial cells ([name] et al., unpublished data). The key question is whether the efficiency of binding by patient isolates is related to their ability to cause disease or the efficiency at which they do so. The present study will address this key question by modelling sequestration *in vitro* using human organ-derived endothelia, and clinical *P. falciparum* isolates from children with cerebral and uncomplicated malaria, and characterised laboratory isolates. We hypothesise that *P. falciparum* isolates from patients with cerebral malaria will bind endothelia more efficiently than those from patients with uncomplicated disease.

**Methods**

**(a) Modelling sequestration using human organ-derived endothelia and clinical *P. falciparum* isolates**

A panel of 30 fresh venous blood samples (15 from cerebral and 15 from uncomplicated malaria patients), with parasitemias of 1% or more on thin blood film examination, will be collected from paediatric patients on presentation or at admission. All blood samples will be stored as multiple stabilates in liquid nitrogen and the experiments will not be performed until all the 30 samples have been collected so that the samples can be matched in our experiments for comparison. Each of the 15 patient isolates from cerebral malaria cases will be tested against all the patient isolates from uncomplicated cases in a 15 x 15 matrix in terms of their efficiency of binding to human microvascular endothelial cells (HDMEC) and human umbilical vein endothelial cells (HUVEC).

**(b) Modelling sequestration using human organ-derived endothelia and clinicaland laboratory *P. falciparum* isolates**

A total of 200 *P. falciparum* patient isolates will be collected over a period of 3 years, 100 from patients with uncomplicated malaria and 100 from cerebral malaria patients. Each patient isolate will be matched with four characterised laboratory-adapted isolates. Adhesion to HUVEC and HDMEC will be investigated using *in vitro* static assays using fresh isolates only.

**Statistical analysis**

Absolute numbers of adherent parasitised red blood cells (pRBCs) from the two patient isolates being compared will be counted in 5 fields of the microslide in part (a) and in 3 fields of the coverslip in part (b). To compare the level of adhesion between paired isolates, the number of adherent pRBCs will be expressed per mm2. To compare the level of adhesion between experiments using different pairs of patient isolates, the number of adherent pRBCs/mm2 will be further expressed as the mean number of adherent pRBC/mm2. Statistical differences in adhesion between isolates from uncomplicated and cerebral malaria patients, in part (a), will be tested using a Student’s paired t-test. [name] project looked at competition between the four laboratory isolates that will be used in the current project such that their efficiency to bind endothelia was ranked. Adhesion between uncomplicated and severe patient isolates, in part (b) of this study will therefore be compared based on this information.

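### Part (a) of the adhesion substudy applies a paired t-test to a fully crossed 15 x 15 design without stating the unit of analysis or allowing for reuse of each isolate

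*Protocol*

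**What the plan says.** All of this stands in Protocol section 4.4, under the endothelial adhesion and malaria pathology substudy.

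- **Hypothesis (Background).** It concerns disease groups: "isolates from patients with cerebral malaria will bind endothelia more efficiently than those from patients with uncomplicated disease".
- **Design (Methods, part (a)).** The material is "A panel of 30 fresh venous blood samples (15 from cerebral and 15 from uncomplicated malaria patients"). Each cerebral isolate "will be tested against all the patient isolates from uncomplicated cases in a 15 x 15 matrix", and binding is assessed on two cell types, HDMEC and HUVEC.
- **Measurement (Statistical analysis).** Adherent cells from the two isolates under comparison "will be counted in 5 fields of the microslide in part (a") and expressed per mm². For comparison across experiments with different pairs, the count "will be further expressed as the mean number of adherent pRBC/mm2". The text does not say whether that mean is over the fields of one experiment or over all pairings of one isolate.
- **Test (Statistical analysis).** "Statistical differences in adhesion between isolates from uncomplicated and cerebral malaria patients, in part (a), will be tested using a" Student's paired t-test.

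The substudy text gives no significance level, sidedness, variance component, number of pairs entering the test, or term for repeated use of an isolate.

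**The concern.** The hypothesis is about patients' isolates, so the independent replicates are the 30 isolates, 15 in each group. The matrix produces 225 differences from them. An isolate that happens to bind strongly raises all 15 differences in which it appears. A paired t-test over the matrix treats those 15 as separate evidence, so its standard error shrinks with the number of pairings and not with the number of isolates.

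Chance differences between individual isolates could then be reported as a cerebral-versus-uncomplicated effect. A fully crossed matrix also has no one-to-one pairing between the two groups, so no pairing that follows from the design reduces the data to 15 independent pairs. What is at stake is the only stated test for part (a).

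**Working it through.** The plan states no power, sample-size or error-rate figure for the substudy, so there is none to reproduce. The check asks what the named test does under each way of feeding it the data.

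**Inputs from the Protocol:** 15 isolates per group, fully crossed, 15 x 15 = 225 pairings per cell type, paired t-test.

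**Assumptions, not in the Protocol:** two-sided 5% test; ICC shown over its whole range, 0 to 1; an isolate's binding does not depend on which isolate it is run against.

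**Model with no group difference.** Scale the variance of one adhesion value to 1. The difference for cerebral isolate i and uncomplicated isolate j is d_ij = a_i − b_j + e_ij, with Var(a) = Var(b) = ICC and Var(e) = 2(1 − ICC). An effect shared by both isolates on a slide cancels in d_ij.

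**1. All 225 pairs entered**
- True variance of the mean difference: ICC/15 + ICC/15 + 2(1 − ICC)/225 = 2(1 + 14·ICC)/225.
- Variance the test uses: about 2/225.
- Ratio: about 1 + 14·ICC. At most it is 15, so the standard error is too small by up to √15 = 3.9-fold.
- Approximate false-positive rate: 2·[1 − Φ(1.96/√(1 + 14·ICC))].

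| ICC | Ratio | Formula | Simulated (20,000 runs) |
|---|---|---|---|
| 0 | 1.0 | 5.0% | 4.7% |
| 0.05 | 1.7 | 13.3% | 13.1% |
| 0.1 | 2.4 | 20.6% | 20.3% |
| 0.2 | 3.8 | 31.5% | 32.5% |
| 0.5 | 8.0 | 48.8% | 49.8% |
| 1 | 15.0 | 61.3% | 62.5% |

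The simulation runs slightly above the formula at high ICC because the sample variance of crossed differences is itself a little too small, by the factor 1 − ICC/16. At ICC 1 the ratio is then 15/(15/16) = 16, and 2·[1 − Φ(1.96/4)] = 62.4%.

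These are two-sided rejections under a symmetric null, so half favour the cerebral group: 32.5%/2 = about 16% at ICC 0.2 and 62.5%/2 = about 31% at ICC 1, against a nominal 2.5%.

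**2. Fifteen row differences entered** (each cerebral isolate minus the mean of its 15 opponents)
- Variance the test uses: [ICC + 2(1 − ICC)/15]/15 = (2 + 13·ICC)/225.
- Ratio: (2 + 28·ICC)/(2 + 13·ICC), which is 7.6/4.6 = 1.65 at ICC 0.2 and 30/15 = 2 at ICC 1.
- Simulated false-positive rate: about 12% at ICC 0.2 and 15% at ICC 1. Variation among the uncomplicated isolates is still left out.

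**3. One mean per isolate entered, 15 against 15**
- Simulated false-positive rate: 4.8% to 5.2% at every ICC, for a two-sample t-test and equally for a t-test on arbitrarily paired isolate means.

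The three readings therefore give very different error rates, and the text does not say which is meant.

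**The case against.** The strongest reply is that the protocol never says the 225 pairs are entered. The sentence just before the test speaks of a mean used to compare experiments with different pairs. If that is a mean per isolate, the test holds its level. This stands as far as it goes: the defect is an unstated unit of analysis whose natural reading is invalid, not a stated intention to enter 225 values. It is still the less natural reading. The paragraph works throughout with pairs of isolates, the only averaging it makes visible is over microscope fields, and a paired test on isolate means would need a pairing that the protocol does not define.

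A reader might infer that the plan will produce false positives in a third to two thirds of cases. The documents do not support that. It needs all 225 pairs, a two-sided 5% test and an ICC of about 0.2 to 1, none of which the protocol gives; the top of the range means no assay error at all. Nor would the directional hypothesis be wrongly confirmed that often, since half of the rejections point the other way.

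A reader might also infer that pairing is wrong in itself. It is not: two isolates assessed in the same experiment form a real block. The fault lies in reusing isolates across blocks.

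Finally, part (b), with 100 isolates per group, also compares the disease groups, so part (a) is not the only evidence. The substudy is separately funded and needs no extra specimens. Both points limit the importance but do not repair the test.

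**Conclusion.** The point holds in conditional form. The crossed design and the paired t-test are both written into the protocol, the unit of analysis is not, and nothing allows for each isolate appearing 15 times. If the pairs are entered as they stand, nominal 5% becomes about 13% at an ICC of only 0.05 and rises to 62% at ICC 1. Row differences leave 12% to 15% for ICC 0.2 to 1, and isolate means leave 5%.

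The ICC is unknown. A value near zero would sit oddly with the Background, which reports that laboratory isolates could be ranked by binding efficiency and that only about 80% of patient isolates bound ICAM-1, but neither statement supplies a figure.

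The severity is low to moderate. No objective, endpoint, sample size or safety decision of the main trial depends on this analysis.

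**What to change.** State that the isolate is the unit of analysis in part (a), and replace the paired t-test with one of these, separately for HDMEC and HUVEC:

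- a comparison of the 15 cerebral with the 15 uncomplicated isolate-level means, by two-sample t-test or rank test; or
- a mixed model with crossed random effects for cerebral and uncomplicated isolate, and with experiment or slide as block.

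The Background raises competition between parasite lines on endothelium. If an isolate's count depends on its opponent, the isolate means within a group share that dependence and the two-sample comparison no longer has the right standard error. The crossed model, fitted to the within-pair differences, is then the safer choice. The protocol should also say what the mean adhesion per mm² is averaged over.

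The cost is one sentence and a different analysis of the same data, with no new samples or assays. The standard error becomes wider, and correctly so, which makes significance harder to reach.
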